### Allocation of communication method

There are two types of centres who may be involved in the research: centres who currently deliver benign results in-person and centres who currently deliver benign results by telephone.

For centres currently delivering results in-person, the following process for scheduling a results appointment will be observed: During in-person study months, all consenting women at time point 1 will be given an appointment to re-attend to receive their results in-person and will receive the result in-person. During telephone study months, all consenting women at time point 1 will be given an appointment to re-attend to receive their results in person. However, they will instead be telephoned prior to their scheduled appointment. Only benign women will be telephoned, with all women receiving other results (eg, cancer) attending their scheduled appointment.

For centres currently delivering results by telephone, the following process for scheduling a results appointment will be observed: All consenting women will be informed that, when their results are ready, they will be contacted by telephone to arrange an appointment to come back for their results. During the ‘telephone’ months of the study, women will be telephoned as expected. However, instead of arranging an appointment during this telephone call, results will be delivered. This means that, for women who go on to have a cancer result, they can be telephoned to arrange an appointment to attend in-person, as expected. This is in line with standard practice at these centres. During the in-person months, all consenting women will be informed that, when their results are ready, they will be telephoned to arrange an appointment to come back for their results. These women will be telephoned to arrange an appointment to come back in-person, and at that appointment they will receive their benign/normal result.

All women not enrolled in the study will receive their screening result based on the current standard practice at the attended centre.

### Data collection

#### Time point 1

Participant recruitment at time point 1 will occur concurrently at each breast screening centre.

Women will be approached during their assessment visit by breast care nurses with good clinical practice training. These women would have been recalled from a previous mammogram and may have a biopsy as part of the assessment clinic. The study will be explained to potential participants and nurses will go through the informed consent process. Consenting women will fill out the time point 1 survey with study responses collected and stored securely before the participant leaves the assessment clinic.

#### Multidisciplinary team meeting

At the local-level multidisciplinary team meeting for breast screening staff, women recruited into the study will be included in further time points if they receive a benign (B2) or normal (B1) result. A breast care nurse will compile the contact details of eligible women into a spreadsheet to be sent securely to the research team.

#### Time point 2

The research team will distribute time point 2 surveys to eligible women with a pre-paid return envelope. If no response is received within a week, the research team will contact women by telephone as a reminder. A maximum of two telephone contact attempts will be made. This is to ensure anxiety and understanding are measured at the crucial post-results stage of the screening process.

As part of time point 2 survey, women will be asked if they would like to participate in further research involving an interview about their experience of receiving a screening result.

#### Time point 3

The research team will distribute time point 3 surveys, 3 months after the biopsy result was received.

#### Time point 4

The research team will distribute time point 4 surveys, 6 months after the biopsy result was received.

#### Qualitative telephone interviews

The qualitative telephone interviews will explore why women prefer certain methods of communication. Women will be recruited from the time point 2 survey. Women who express an interest in participating will be sent further information about the interviews. If they wish to participate, women will return the consent form in the pre-paid envelope. Women will then be contacted by telephone by the research team to be interviewed.

The semi-structured telephone interviews will each take 10–20 min. Questions will encompass the woman’s experience of receiving a result from screening. This will involve asking how the woman felt, whether she understood her result and an exploration of her views on different methods for communicating results. Interviews will be audio-recorded and transcribed verbatim. Data collection will cease once no further themes emerge and data saturation is reached.

#### Mixed-methods integration

Using a mixed-methods approach, the quantitative preference survey data will be combined with the findings from the qualitative interviews. The quantitative data ask a binary choice question regarding women’s communication preferences (telephone or in-person), while the qualitative interviews expand on this by exploring how women justify certain preferences for communication. In mixing the data, the qualitative data will be used to *expand* the understanding of the findings from the quantitative surveys.^22^ Expansion provides richness and detail, expanding why and how women form communication preferences and moving understanding of preferences *beyond* what quantitative data or qualitative data in isolation can elucidate. The value added by integrating the knowledge of both *what* women prefer and *why* is in the completeness of our understanding of preferences, making the evidence that will inform the NHSBSP policy decisions comprehensive and patient-centred.

### Sample size considerations

In order to determine the sample size for a clustered randomised crossover study, a full specification of the important within-cluster (centre) between-period and within-period correlations is required.^23^ There is currently no available evidence on the magnitude of these correlations in our selected setting, so rather than arbitrarily selecting values we adopt a conservative approach and assume that the (within-centre) between-period correlations are zero and proceed to power as if the design were a cluster randomised design. Although the crossover aspect of the design is not explicitly accounted for in the sample size calculation, it is incorporated fully in the analysis of the primary study outcome (PCQ anxiety score at time point 2). The aim of the study is to be able to detect a clinically significant difference of 3 points in the PCQ (the difference between the score on one statement being 0, not at all, and 3, quite a lot of the time).

**Figure 1 F1:**
[figure not shown]
Flow of required sample size for the study.

Assuming the primary outcome is approximately normally distributed, and the test is at the 5% significance level with 80% power to detect an effect of the specified size, 194 participants are required at time point 2, that is 97 participants per arm. Allowing for attrition rate between time point 1 and time point 2 due to participant withdrawal (15%) and participant eligibility (50%), a total of 457 participants will be recruited at time point 1. Participant withdrawal was calculated based on a mean response rate of 60% from previous research using postal surveys in a medical setting^24^ with a loss of 15% at each time point as a conservative estimate.

In order to account for clustering due to the recruiting centre, design effect was applied that inflated the sample size. The intra-cluster (within-centre) correlation coefficient was set to be 0.01 and the number of observations within each cluster was assumed to be equal. With the sample size of 194 women, divided by the number of centres^4^ and then divided by the number of interventions,^2^ this led to the number of observations within a cluster to be 48.2. This gave a design effect of 1.49. Taking this into account, the sample size needed to achieve statistical significance (194 women) was multiplied by the design effect, giving a total sample of 290 women at time point 2 when rounded up (see figure 1).

31 926 women are recalled for a biopsy each year. If half of the 31 926 biopsies come back as benign, this leaves a potential sample of 15 963. This means that, on average across 80 breast screening centres, each centre will have around 200 benign biopsy results each year. Therefore, assuming 50% participation rates of eligible women, recruitment will require four centres for 1 year.

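### The only stated recruitment target, 457 at time point 1, omits the clustering allowance: the plan's own requirement of 290 at time point 2 implies 683

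*Protocol article*

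**What the plan says.** All of this stands in the protocol article under *Sample size considerations*, including the text that follows the Figure 1 caption.

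- The effect sought: the study aims to "detect a clinically significant difference of 3 points in the PCQ".
- Error rates: "the test is at the 5% significance level with 80% power to detect an effect of the specified size".
- Requirement before clustering: "194 participants are required at time point 2, that is 97 participants per arm".
- Recruitment: after allowing for 15% withdrawal and for half of recruits proving ineligible, "a total of 457 participants will be recruited at time point 1".
- Clustering, in the next paragraph: "The intra-cluster (within-centre) correlation coefficient was set to be 0.01". A design effect of 1.49 is applied to the 194, "giving a total sample of 290 women at time point 2 when rounded up". Figure 1, described as the flow of the required sample size, is cited at this point.
- Accrual: about 200 benign results per centre per year and 50% participation, from which the plan concludes that four centres are needed for one year.

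The text gives no time point 1 number that corresponds to 290, and it does not revise 457.

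**The concern.** The section gives one number for women to be recruited and one for women needed in the primary analysis, and the first does not produce the second. The loss allowance is applied to 194 and the design effect is also applied to 194, but the two inflations are never combined. A site or oversight body reading the text would take 457 as the point at which enrolment is complete. At that point the plan's own losses leave no allowance for clustering. The 80% power would then not hold on the basis the plan chose, and a null finding on the 3-point difference would be less informative than stated.

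**Working it through.** **Inputs, all from *Sample size considerations*:** 3 PCQ points; 5% significance level; 80% power; 194 women (97 per arm) before clustering; losses of 15% and 50%; design effect 1.49; 290 women after clustering; 457 recruits. The sidedness of the test is not stated, and two-sided is assumed. No standard deviation is stated.

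**1. Reproduce the plan's 457.** 194/(0.85 × 0.50) = 194/0.425 = 456.5, rounded up to 457. This is an exact match.

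**2. Reproduce the plan's 290.** 194 × 1.49 = 289.06, rounded up to 290.

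**3. Can 457 be reached from 290?** The same formula gives 290/0.425 = 682.4, so 683 (684 if rounded up after the 15% step and again after the 50% step). Looser ways of applying the losses also miss 457:

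| Calculation from 290 | Result |
|---|---|
| 290/0.85 | 341 |
| 290 × 1.5 | 435 |
| 290 × 1.15 × 1.5 | 500 |
| 290 × 1.15 × 2 | 667 |
| 290/(1 − 0.65) | 829 |

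So 457 belongs to 194, not to 290.

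**4. What 457 yields.** 457 × 0.85 × 0.50 = 194.2 women at time point 2. The gap is 290 − 194 = 96, or 96/290 = 33%. At time point 1 the gap is 683 − 457 = 226, or 226/457 = 49% more recruits.

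**5. Power if recruitment stopped at 457.** The standardised effect implied by 97 per arm is (1.960 + 0.842) × √(2/97) = 0.402, equivalent to an SD of 3/0.402 ≈ 7.46 points. Effective N is N divided by the design effect, and power is Φ(0.402 × √(n/2) − 1.960), with n the effective number per arm.

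| Women analysed | Design effect | Effective N | Power |
|---|---|---|---|
| 194 | 1.00 | 194 | 80.0% |
| 194 | 1.49 | 130.2 | 63.1% |
| 290 | 1.49 | 194.6 | 80.1% |

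The 63% barely moves if the design effect is recalculated from the plan's cluster size of 48.2: 1 + 47.2 × 0.01 = 1.472 gives 63.7%. The described division, 194/4/2, is in fact 24.25. That gives a design effect of 1.2325 and 71.3% power with 194 women, still below 80%.

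**6. What the accrual plan yields.** 4 × 200 × 50% = 400 participants with a benign result, corresponding to 400/0.50 = 800 at time point 1. After 15% loss, 400 × 0.85 = 340 reach time point 2. With 340 women and a design effect of 1.49, effective N is 228.2 and power is about 86%.

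**The case against.** The strongest case on the other side has four parts.

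*The paragraphs are successive steps.* The plan sizes without clustering first and then inflates, so 290 governs and 457 is an intermediate number left behind. That may be how it arose. But 457 is worded as a commitment to recruit, it is the only time point 1 figure in the text, and nothing replaces it. A superseded number left as the target still needs correcting.

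*Figure 1 may carry the right number.* It is cited beside the 290 and is not shown, so this cannot be excluded. If it does show a figure matching 290, the practical risk is smaller, but text and figure then disagree and must be reconciled.

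*Recruitment is planned by duration.* A reader might infer that the trial will be underpowered, or was planned with no clustering allowance. The documents do not support either inference. The plan does inflate for clustering at time point 2. It describes four centres for a year, and no sentence says enrolment ends at 457. On its own rates, a full year gives about 340 women, above 290. This objection stands and makes the shortfall conditional.

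*The 63% is not the power of the planned analysis.* The plan sets between-period correlation to zero, calls this conservative, and says the crossover is incorporated in the analysis; the primary model also adjusts for baseline PCQ. As an illustration only, an assumed baseline correlation of 0.3 to 0.6, which the documents do not give, would put power with 194 women at about 67% to 82% at a design effect of 1.49. So the true power with 194 women is not established. But the plan declines to count the crossover gain and states 290 as its requirement, so these gains cannot justify a target that yields 194.

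**Conclusion.** The inconsistency holds and should be corrected. The stated recruitment target of 457 is computed before clustering, whereas the stated requirement of 290 is computed after it; 683 recruits correspond to 290 under the plan's own losses. Recruiting exactly 457 would leave about 194 women, 96 short.

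The fall in power, from 80% to about 63%, is conditional on recruitment stopping at 457. It rests on the plan's design effect of 1.49, a two-sided 5% test, and the standardised effect of about 0.40 back-calculated from 97 per arm. It is a figure on the plan's own planning basis, not a forecast for the trial. The arithmetic in the text is certain; what Figure 1 shows is not known.

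**What to change.** Take one of two routes:

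1. Restate the time point 1 target as 290/(0.85 × 0.50) = 683, and make the text and Figure 1 agree.
2. Keep 457, and state that it yields about 194 women at time point 2, with the lower power that follows.

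The first costs one number in the text and, if needed, one in the figure. The plan's own accrual of about 800 at time point 1 over the year already exceeds 683, so no further centre is implied, and neither design nor analysis changes.

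The cluster size and design effect need a separate check, since 194/4/2 is not 48.2. If they are corrected, recompute the time point 2 and time point 1 figures together, with cluster size updated for the final sample. A tempting shortcut is to hold cluster size at 24.25, giving 194 × 1.2325 = 239.1, so 240 women, and 240/0.425 = 565 recruits. Those figures should not be used: 240 women in eight centre-by-method cells give cluster size 30, a design effect of 1 + 29 × 0.01 = 1.29, effective N of 186 and power of about 78%, below the stated 80%.

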### Participants and settings

This trial will be conducted in a breast screening centre setting. The study will take place in the UK where women are invited to attend breast screening every 3 years for digital mammography. The study will take place across four time points (see table 1) with a survey completed by participants at each stage. The study participants will be recruited from four English Breast Screening centres across different regions.

**Table 1 T1:** Time points for the study

Time point	Sample	Survey content	Method
Time point 1—at assessment clinic	Women attending assessment follow-up clinic	Demographic information Communication preferences Baseline anxiety score (PCQ) Contact details	In-person
Time point 2—after receiving results	Women from time point 1 who had a normal or benign biopsy	Communication preferences Repeat anxiety score (PCQ) Measure of understanding	By post
Time point 3—3-month follow-up	Women from time point 1 who had a normal or benign biopsy	Repeat anxiety score (PCQ)	By post
Time point 4—6-month follow-up	Women from time point 1 who had a normal or benign biopsy	Repeat anxiety score (PCQ)	By post

PCQ, Psychological Consequences Questionnaire.

Participants will be women between the ages of 47 and 73 attending the NHSBSP for further tests following a suspicious mammogram. This includes women offered routine screening between ages 50 and 70 and those receiving extra rounds of screening between the ages of 47 and 49 or 71 and 73 as part of the UK age extension trial.^16^ Women will be recruited at the assessment clinic pre-biopsy. However, only women who have received a benign (B2) or normal (B1) biopsy result will be included in the longitudinal data collection. Participants will not be included in the study if they presented symptomatically to the breast clinic, if they are not the recommended screening age, if they do not receive a biopsy, if they do not have English as a first or second language and if they do not have the capacity to consent.

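### The printed cluster size (48.2), design effect (1.49) and 290 women at time point 2 do not follow from the stated inputs; the steps described give 24.25, 1.23 and 240

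*Protocol article*

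**What the plan says.** All of this stands in the protocol article under Sample size considerations, including the text after Figure 1.

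- Target: to "detect a clinically significant difference of 3 points in the PCQ"; "the test is at the 5% significance level with 80% power to detect an effect of the specified size". On that basis "194 participants are required at time point 2, that is 97 participants per arm". No SD is printed.
- Correlation structure: the authors "assume that the (within-centre) between-period correlations are zero and proceed to power as if the design were a cluster randomised design".
- Clustering: "The intra-cluster (within-centre) correlation coefficient was set to be 0.01". The 194 women are divided by the number of centres and then by the number of interventions, and "this led to the number of observations within a cluster to be 48.2". Next: "This gave a design effect of 1.49". Multiplying 194 by this gives 290 women at time point 2.
- Recruitment: 457 women at time point 1, allowing for 15% withdrawal and 50% eligibility.

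**The concern.** The paragraph prints its inputs, its operations and its results, and they disagree at two consecutive steps. The cluster size is about twice what the described division gives, and the design effect does not match the printed cluster size. The figure of 290 inherits both discrepancies.

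A reader therefore cannot tell what cluster the authors had in mind (the whole centre, or the centre under one communication method), how many women the primary comparison needs, or what power 290 provides. Anyone who judges the trial's size, or reuses the calculation for another cluster crossover trial, would start from a number that the stated method does not produce.

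**Working it through.** **Inputs.** Unadjusted total 194 (97 per arm), ICC 0.01, between-period correlation 0, difference 3 PCQ points, 5% level (taken as two-sided, since the article does not say) and 80% power, all from Sample size considerations. The two divisors print as superscripts, like citation marks. Their values are clear all the same: Participants and settings says women will be "recruited from four English Breast Screening centres across different regions", and there are two methods, telephone and in-person.

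**The plan's last step reproduces.** 194 × 1.49 = 289.06, rounded up to 290.

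**The cluster size does not.** 194/4/2 = 24.25. Dividing by 4 only gives 48.5, so the division by 2 appears not to have been carried out, and 48.2 may be a misprint of 48.5.

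**The design effect does not.** The usual formula is DE = 1 + (m − 1) × ICC, and N = 194 × DE rounded up. For power at 290, the SD is back-calculated from 97 per arm: SD = 3 / [(1.96 + 0.84) × √(2/97)] ≈ 7.46. Power is then Φ(3 / (SD × √(4 × DE/290)) − 1.96).

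| Cluster size m | DE | N at time point 2 | Power at 290 |
|---|---|---|---|
| 24.25 (194/4/2, as described) | 1.2325 | 239.1 → 240 | 87.0% |
| 36.25 (290/8, cell size when 290 are analysed) | 1.3525 | – | 83.8% |
| 48.2 (as printed) | 1.472 | 285.6 → 286 | 80.6% |
| 48.5 (194/4 only) | 1.475 | 286.15 → 287 | 80.5% |
| 50 (needed for 1.49) | 1.49 | 289.06 → 290 | 80.1% |

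The nearest route from the text to 1.49 leaves out the −1: 1 + 48.5 × 0.01 = 1.485, rounded up. That is a guess at the origin; the article does not show it.

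**Size of the discrepancy.** 290 − 240 = 50 women, or 50/240 ≈ 21% above what the described steps give. The 240 takes m from the total before inflation, as the article does. If m is allowed to grow with the total (m = N/8), then N = 194 × 0.99 / (1 − 194 × 0.01/8) = 253.5, so 254, which is still below 290.

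**Time point 1.** 194/0.85/0.5 = 456.5, so 457: the printed total is built on 194 without the design effect. On the same allowances 240 would imply 240/0.85/0.5 = 564.7, so 565, and 290 would imply 682.4, so 683. Conversely, 457 × 0.85 × 0.5 ≈ 194 women at time point 2. With 194 women in eight cells m is exactly 24.25, and power with DE 1.2325 is about 71%.

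**The case against.** The best defence is that the slip does no harm to power at 290. It enlarges the requirement, and power at 290 stays above 80% for every cluster size that the described or printed steps could yield. The step from 48.2 to 1.49 taken alone is minor: 286 against 290. The concept is also sound. Dividing by centres and by interventions treats the centre-by-intervention cell as the cluster, which fits a between-period correlation of zero. Because methods alternate monthly, such a cell is larger than a single centre-month, so the choice is cautious. All of this stands. What it does not rescue is the derivation: the division was described correctly and its result was reported wrongly.

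Two stronger readings are tempting, and the documents support neither.

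- A reader might infer that the trial is underpowered at 290, because the article powers it as if it were cluster randomised and the printed cluster size is close to a whole centre's share of 194. But the article divides by interventions as well as by centres, every centre delivers both methods (Randomisation and blinding, Table 2), and the primary model includes centre and period effects. A parallel trial of four whole centres is neither what is run nor the division described. The 80% in the text is, moreover, attached to the unadjusted 194.
- A reader might infer that the recruitment plan rests on 290. The stated time point 1 total of 457 rests on 194.

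**Conclusion.** The point holds as an error of derivation. On the stated inputs the cluster size is 24.25, the design effect 1.2325 and the requirement 240 women at time point 2, against the printed 48.2, 1.49 and 290. The error is conservative on the plan's own formula, and no loss of power at 290 is claimed. The primary analysis is not affected.

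The same section also leaves two time point 2 numbers unreconciled: 290 after the design effect, and about 194 as the yield of the 457 to be recruited.

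The power figures assume a two-sided 5% test, the back-calculated SD of about 7.46, ICC 0.01, equal cell sizes, and a normal approximation that makes no allowance for the small number of clusters. Because no SD is printed, 194 itself could not be checked. Figure 1, which shows the sample-size flow, was not available.

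**What to change.** Under Sample size considerations:

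1. Correct the cluster size to 24.25 and the design effect to 1.23, and say that the cluster is the centre-by-intervention cell, in line with the assumed zero between-period correlation.
2. Either restate the time point 2 requirement as 240, or keep 290 as a declared margin and give its power (about 84% with m = 290/8), with the SD used.
3. Reconcile the result with the time point 1 total. If 457 is kept, state that it yields about 194 women at time point 2 and give the power after clustering (about 71% on the assumptions above), rather than enrolling more. If a design effect is meant to apply at time point 1, the totals that follow are 565 (from 240) or 683 (from 290).
4. Make Figure 1 agree with whichever numbers are kept.

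The cost is a recalculation and a few sentences. Keeping 457 with its power stated needs no additional participants.

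### The design effect is taken at the cluster size before inflation while the centres are fixed at four, so 290 women and 80% power do not correspond; whether 290 is too few or more than enough depends on the cluster meant

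*Protocol article*

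**What the plan says.** All of this is in the protocol article, Sample size considerations, unless noted.

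- The aim is to "detect a clinically significant difference of 3 points in the PCQ", where "the test is at the 5% significance level with 80% power to detect an effect of the specified size". Without clustering, "194 participants are required at time point 2, that is 97 participants per arm".
- Correlations between periods within a centre are taken as zero, and the authors "proceed to power as if the design were a cluster randomised design".
- "The intra-cluster (within-centre) correlation coefficient was set to be 0.01", with clusters of equal size.
- The cluster size starts from the uninflated number: "With the sample size of 194 women, divided by the number of centres", and then by the two interventions. It is stated as 48.2, with a design effect of 1.49.
- Then "the sample size needed to achieve statistical significance (194 women) was multiplied by the design effect", which gives 290 women at time point 2.
- The number of centres does not change: Participants and settings names four, and the recruitment estimate concludes that "recruitment will require four centres for 1 year".

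**The concern.** A design effect of 1 + (m - 1) × ICC has to be evaluated at the cluster size m that the trial will have. Multiplying once is correct when m is fixed and the extra participants come from new clusters. Here the clusters are fixed and m grows. Going from 194 to 290 women makes every cluster about half as large again, so the design effect at 290 is larger than the one used to reach 290. The plan does not go back and recompute it.

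This is a separate matter from the division in the same paragraph, where 194 divided by 4 and by 2 is 24.25, not 48.2. Correcting that division leaves the method unchanged, and the corrected figure would again be evaluated at the wrong cluster size. What is at stake is whether the stated sample size and power, two headline design properties, follow from the stated inputs.

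**Working it through.** **Inputs from the plan:** 194 women before clustering (97 per arm), difference 3 points, 5% level, 80% power, ICC 0.01, four centres, two methods. **Assumptions:** a two-sided test, since sidedness is not stated. The SD is not stated either; 97 per arm implies 3 × √(97/2) / (1.960 + 0.842) = 7.46, and it cancels from the power comparisons below.

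**Step 1. Reproduce the plan's figure.** 194 × 1.49 = 289.06, rounded up to 290. The design effect of 1.49 belongs to clusters the size of a whole centre: 194/4 = 48.5 gives 1 + 47.5 × 0.01 = 1.475, and the stated 48.2 gives 1.472. The remaining gap to 1.49 is small. The division as described, 194/4/2 = 24.25, gives 1 + 23.25 × 0.01 = 1.2325 and 194 × 1.2325 = 239.1, so 240 women. That does not reproduce 290.

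**Step 2. Power of 290 at its own cluster size.** With k clusters, m = n/k, DE = 1 + (m - 1) × 0.01, effective n = n/DE, and power = Φ(2.802 × √(effective n / 194) - 1.960).

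| Women | Clusters k | m | DE | Effective n | Power |
|---|---|---|---|---|---|
| 290 | 4 whole centres | 72.5 | 1.715 | 169.1 | 74.4% |
| 290 | 8 centre-by-method cells | 36.25 | 1.3525 | 214.4 | 83.8% |
| 240 | 8 centre-by-method cells | 30 | 1.29 | 186.0 | 78.3% |

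The last row is the result of correcting only the division.

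**Step 3. Number that gives 80% power with k fixed.** Solve n = 194 × [1 + (n/k - 1) × 0.01], that is, n = 194 × 0.99 / (1 - 1.94/k).

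- k = 8: 192.06 / 0.7575 = 253.5, so 254 women.
- k = 4: 192.06 / 0.515 = 372.9, so 373 women.

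**Step 4. Centre-months as clusters.** If women seen in different months at a centre are uncorrelated, the cluster is the centre-month. Over one year at four centres there are 48. For 290 women, m = 6.04, DE = 1.05, effective n is about 276 and power is about 92%. The one-step number would be 200 and the fixed-k number 201. With the 24 centre-months of the six months in Table 2, the two numbers are 208 and 209.

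**The case against.** The strongest reply is that the error is small or harmless once the cluster is properly defined. The text divides by centres and then by interventions, which means eight cells, and on that basis 290 exceeds the 254 needed. The whole-centre basis is hard to defend in this design. The plan assumes zero correlation between periods, and every centre alternates the two methods monthly, so a centre effect is shared by both arms. With centre-months as clusters, the one-step and fixed-k numbers differ by a single woman. The calculation also takes no credit for baseline adjustment, and the plan says there is no evidence on the size of the correlations.

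Much of this stands. A reader might infer from the 74% and 373 figures that the trial is underpowered or should recruit more. The document does not support that inference: those figures need the whole centre to be the cluster, which matches 48.2 and 1.49 and the choice to power as a cluster randomised design, but sits badly with the zero between-period correlation.

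The reply does not restore the stated pair, however. On none of these bases do 290 women give 80% power. Nor can the roughly 92% for centre-months be used to defend the figure as written, because the section says that the crossover was not explicitly accounted for in the calculation.

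**Conclusion.** The concern holds in a limited form. The design effect is evaluated before inflation with the number of centres fixed, so 290 women and 80% power do not correspond under the plan's own formula. The direction is open. With eight cells 290 is more than enough, by 36 women (290 - 254) and about 4 percentage points of power. With four whole centres it is short by 83 women (373 - 290) and about 6 points. If only the division were corrected, the resulting 240 would be 14 women short of 254, with about 78% power.

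These results assume a two-sided 5% test, equal cluster sizes and an ICC of 0.01. Like the plan's calculation, they make no allowance for the small number of clusters or for baseline adjustment.

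**What to change.** Revise the sample size paragraph in three steps.

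1. State which cluster is meant, reconcile it with the assumption of zero between-period correlation, and correct the division so that the wording and the cluster size agree.
2. With k fixed, replace the single multiplication by the solution of n = 194 × [1 + (n/k - 1) × 0.01], so that the design effect is the one at the final cluster size.
3. Keep 290 and restate its power for the chosen k: about 84% for eight centre-by-method cells, or about 74% for four whole centres. If the centre-month is chosen, show that calculation explicitly.

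The cost is one reworded paragraph and one restated power figure. Enrolment and trial conduct do not change.
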